### Effect size

To quantify the effects, partial η-square values will be calculated using cut-off-norms provided by Cohen [77]. In advantage to Cohen’s d, the amount of differential effect in the interaction model can be quantified. Subgroup differences will also be quantified using partial η-square values.

All statistical analyses will be conducted using either SPSS version 21 (SPSS Inc., Chicago, IL, USA) or Microsoft Office Excel (Microsoft Corporation, Redmond, WA, USA)

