**Methods/Design:**

This study protocol presents a prospective randomized controlled trial, involving four assessment time points: baseline, post-intervention, one-year follow-up and five-year follow-up. The aims include evaluating the effect on stress, coping, psychological morbidity and personality traits with validated measures. Participants are allocated randomly to one of three conditions: MediMind, Autogenic Training or control group. Eligible participants are medical or dental students in the second or eighth semester of a German university. They form a population of approximately 420 students in each academic term. A final total sample size of 126 (at five-year follow-up) is targeted. The trainings (MediMind and Autogenic Training) comprise five weekly sessions lasting 90 minutes each. MediMind will be offered to participants of the control group once the five-year follow-up is completed. The allotment is randomized with a stratified allocation ratio by course of studies, semester, and gender. After descriptive statistics have been evaluated, inferential statistical analysis will be carried out with a repeated measures ANOVA-design with interactions between time and group. Effect sizes will be calculated using partial η-square values.

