## Methods/Design

### Trial design

This is a prospective, randomized, controlled trial, involving four assessment time points (baseline, post-intervention, one-year follow-up and five-year follow-up) and three groups (experimental treatment, standard treatment and control without treatment). Participants are a self-selected group that will be assigned randomly to either the experimental, standard or control group. The longitudinal design will allow the evaluation of the short- and long-term effects of the intervention. Figure 1 shows the overall design of this project. All study procedures, written information and consent forms received approval from the local ethics committee (Landesärztekammer Rheinland-Pfalz, file number: 837.380.13/9065-F) and the University Medical Center data protection official. To report this randomized controlled trial we made use of the CONSORT guidelines [52,53].

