### Statistical methods

Descriptive statistics on study population will be calculated for each group at baseline. Means and standard deviations on primary, co-primary, secondary outcome and additional measures will be presented at baseline, post intervention and at the two follow-up time points for each group. A two-folded approach according to Tabachnik and Fidell [75] is used to address missing data. Initially, a Completer-Analysis with a sample of complete data-sets of each person is evaluated. Secondly, an Intent-to-Treat-Analysis with a Last-Observation-Carried-Forward-Method will be applied to check for differences and possible drop-out-effects. The null hypothesis will be rejected at the cut-off of 5% (α-level), therefore a *P* value ≤ .05 will be applied. To evaluate all group x time interactions in one model, we will use an explicatory MANOVA with primary, co-primary and secondary outcome. We expect differential time x group effects on secondary outcome at the one year/five year follow-up after post-intervention assessment. Therefore, this preliminary analysis will be called ‘explicatory’. For confirmatory analysis following the assumption that primary and co-primary outcome are separate hypothesis, both hypotheses will be tested in separate repeated-measures ANOVA’s with the factorial structure group (MediMind, Autogenic Training and control group) x time. The hypothesis will be evaluated through testing interaction effects. Orthogonally constructed comparisons are then used to check for pairwise differences. If needed, Holm-Bonferroni corrected pairwise comparisons will be used [76]. Additionally post-hoc sub-group comparisons (sex, semester, cohort) will be conducted to analyze data sets furthermore.

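### Grading the group x time partial eta-square with Cohen's cut-offs gives size labels that depend on retest correlation and number of waves as well as on the difference between arms

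*Protocol article*

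**What the plan says.** The confirmatory analysis is set out in the Statistical methods section of the protocol article. For the primary outcome (TICS) and the co-primary outcome (Brief COPE), "both hypotheses will be tested in separate repeated-measures ANOVA’s with the factorial structure group (MediMind, Autogenic Training and control group) x time". The term that carries the inference is also fixed: "The hypothesis will be evaluated through testing interaction effects".

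The Effect size section then says how large an effect will be called: "To quantify the effects, partial η-square values will be calculated using cut-off-norms provided by Cohen". It gives a reason for the choice: "In advantage to Cohen’s d, the amount of differential effect in the interaction model can be quantified". Subgroup differences are to be quantified in the same way. The abstract repeats the metric: "Effect sizes will be calculated using partial η-square values". No other effect-size measure is named, and neither the cut-off values nor any retest correlation is printed.

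Two further commitments in Statistical methods bear on the point. Means and SDs will be given for each group at all four time points. The interaction test will be followed by orthogonal contrasts and, if needed, Holm-Bonferroni pairwise comparisons.

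**The concern.** A size label should follow how far the arms differ. Cohen's norms for eta-square, as assumed here, match standardised differences of roughly 0.2, 0.5 and 0.8 when the denominator contains the full between-person variance. In a repeated-measures interaction that variance has been removed and only within-person error remains. The label then depends on two features unrelated to the benefit: how strongly the scale correlates with itself over time, and how many waves are in the model.

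Three consequences follow for this trial.

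- The same difference between arms can earn different labels on TICS, Brief COPE and BSI simply because their retest correlations differ.
- If results are analysed as the follow-up waves arrive, an undiminished benefit can be graded lower each time. Durability at one year is a stated aim in the section on the concept of mindfulness.
- The three-arm interaction value is an omnibus figure. It does not show whether MediMind or Autogenic Training produced the effect, while the hypothesis under Primary and secondary aim is that MediMind is superior to both comparators.

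**Working it through.** The article prints no partial eta-square, so there is no figure of the plan's own to reproduce on this point.

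**Inputs from the article.** Allocation 2:2:1, so the arm shares are 0.4, 0.4 and 0.2 (Randomization). Four assessments (Trial design). The levels of time in the confirmatory ANOVA are not stated, so two, three and four waves are shown.

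**Assumptions.** Cut-offs 0.01 small, 0.06 medium, 0.14 large. Retest correlation r from 0.3 to 0.9. Compound symmetry, SD 1 in every arm. MediMind better by d than both other arms at every post-baseline wave.

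**Formula.** With m waves, per participant:

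- Interaction sum of squares = 0.4 × 0.6 × d² × (m − 1)/m = 0.24 d² (m − 1)/m
- Within-person error = (m − 1)(1 − r)
- Partial eta-square = 0.24 d² / [0.24 d² + m(1 − r)]

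The between-person eta-square for the same arm means at a single wave is 0.24 d² / (0.24 d² + 1). The two agree only when m(1 − r) = 1, which at four waves means r = 0.75. Below that r the planned figure is the smaller of the two, and above it the larger.

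**Four waves.** For d = 0.5, 0.24 d² = 0.06. For d = 0.8, 0.24 d² = 0.1536.

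| r | d = 0.5 | label | d = 0.8 | label |
|---|---|---|---|---|
| 0.3 | 0.06/2.86 = 0.021 | small | 0.1536/2.9536 = 0.052 | small |
| 0.5 | 0.06/2.06 = 0.029 | small | 0.1536/2.1536 = 0.071 | medium |
| 0.7 | 0.06/1.26 = 0.048 | small | 0.1536/1.3536 = 0.113 | medium |
| 0.8 | 0.06/0.86 = 0.070 | medium | 0.1536/0.9536 = 0.161 | large |
| 0.9 | 0.06/0.46 = 0.130 | medium | 0.1536/0.5536 = 0.277 | large |

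The single-wave between-person values are 0.06/1.06 = 0.057 and 0.1536/1.1536 = 0.133, whatever r is.

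**Changing the number of waves.** d = 0.5 at every post-baseline wave, r = 0.7:

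- Two waves: 0.06/(0.06 + 0.6) = 0.091, medium
- Three waves: 0.06/(0.06 + 0.9) = 0.0625, just medium
- Four waves: 0.06/(0.06 + 1.2) = 0.048, small

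The true difference is constant throughout.

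**Which arm benefits.** MediMind and Autogenic Training have the same share (0.4). If Autogenic Training alone were 0.5 SD better, the interaction sum of squares would again be 0.24 d² (m − 1)/m, and every value above would be the same.

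**Simulation check.** With arms of 50, 50 and 25 and 2,000 runs, mean sample values agreed with those expected at that sample size: 0.244 against 0.245 for d = 0.5, two waves, r = 0.9; and 0.037 against 0.037 for d = 0.5, four waves, r = 0.3. Sample values lie somewhat above the population values (0.231 and 0.021) because partial eta-square is biased upwards.

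**The case against.** The best defence is that the consequence is limited to wording. The hypotheses are decided by the interaction test and the comparisons after it. No alpha, sample size or success criterion depends on a Cohen label. Readers will have group means and SDs at every wave and can work out a standardised difference themselves. All of this stands, and it limits the weight of the point.

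The article's remark about Cohen's d is also literally right. An interaction with three arms and several waves has no single d, and partial eta-square does quantify that omnibus term. What does not follow is that the omnibus value can be graded on norms that presuppose a different denominator.

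A reader might go further and infer that a half-SD effect could be labelled anything from small to large in this trial. The documents do not support that at the four waves of the design. The population value for 0.5 SD stays between 0.021 and 0.130 over r = 0.3 to 0.9. Reaching 0.14 needs r of about 0.91 at four waves, or about 0.82 with only two, and correlations that high are hard to expect over one to five years. Individual trials at r = 0.9 may exceed 0.14, but that reflects upward sampling bias (expected sample value 0.145) over a population value of 0.130. Nor does the article say that its partial eta-squares will be set against the published mindfulness effect of 0.5 that it cites as background.

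The cut-offs and correlations are assumptions, and so is the scenario in which Autogenic Training does no better than control. If Autogenic Training had half of MediMind's benefit, the between-arm factor would be 0.14 d² instead of 0.24 d². The four-wave values for 0.5 SD would then be 0.035/2.835 = 0.012 to 0.035/0.435 = 0.080. The level changes, but the dependence on r does not.

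**Conclusion.** The point holds as a reporting defect. The article commits itself to a grading rule whose labels do not track the difference between arms and whose omnibus value does not identify the arm that benefits. With the design fixed at four waves, a true 0.5 SD difference is graded small or medium, and a true 0.8 SD difference small, medium or large, according to the retest correlation alone. The apparent fading across two, three and four waves is conditional: it arises if the analysis is run with different numbers of time levels, which the article leaves open.

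The sizes rest on the assumed cut-offs, compound symmetry, equal SDs and a constant advantage of MediMind over both other arms. The qualitative result needs only that between-person variance is absent from the denominator. It would be wrong to conclude that the confirmatory tests, the error rate or the sample size are compromised.

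**What to change.** In the Effect size section, stop applying Cohen's cut-offs to the interaction partial eta-square. The statistic may stay as an ungraded descriptive figure.

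For TICS, Brief COPE and BSI, report two contrasts at each post-baseline wave: MediMind minus Autogenic Training, and MediMind minus control. Give each in scale points and divided by the pooled baseline SD, with 95% confidence intervals. Attach any small, medium or large wording only to these standardised differences.

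The change needs no new data and leaves the tests as they are. It costs a few more output lines per outcome and the loss of a single summary label.

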## Discussion

Our study is the first to evaluate the effectiveness of a mindfulness-based intervention for medical students in Germany in a randomized controlled setting with both treatment groups, MediMind and Autogenic Training, and a control group without treatment. With the possibility of controlling several confounding aspects, the analysis will be based on an experimental design with good power.

One possible limitation of the study might be a motivational bias of the selected participants. It can be assumed that mainly highly motivated students volunteer to take part in a weekly training with an additional time requirement beside the high workload of their curriculum. Possibilities to generalize the results may be limited to students of high motivation and interest in the concept of mindfulness and Autogenic Training. Furthermore, the response rate at the time of post-intervention might be affected as the data cannot be collected directly at the end of the last training session. The students will be asked to send back a paper-and-pencil version of the questionnaire or to complete an online version. Considering the fact that participants of the control group do not benefit from the training until the data collection is completed after five years, the motivation of this specific study group to complete the questionnaires at post-evaluation is expected to be challenging. Further drop-outs could occur one year or five years post-intervention, as participants will be harder to reach or no longer motivated. In order to minimize a reduction in sample size, monetary vouchers will be raffled among the participants. Another limiting effect might be the inclusion of students at different stages of their studies. The experience of stress might differ between the second and eighth semester, and therefore, the effect size of a pre-post effect of the intervention is supposed to be smaller in the advanced semester.

In spite of possible limitations, this study will be one of the few attempts to explore the possibility of stress prevention in a German medical school. In order to address limitations of previous research and to correspond to the demands called for in reviews of the literature [13-15], we use a rigorous study design. Therefore, a strength of our project is the three-group design and the randomized assignment of participants to treatment and control groups. Taking into account the capabilities of implementing a stress prevention training in the medical curriculum, it seems to be more realistic to anticipate a voluntary participation. In that case, our study design reflects a naturalistic setting. Follow-up assessments and the use of validated outcome measures will enable us to ascertain the prevention effect of our intervention. Moreover, the inclusion of students of the second and eighth semester will allow us to compare the impact of intervention at different stages of medical training. By exploring personality traits assumed to work as specific risk factors in medical training, we hope to point out whether a stress prevention training like MediMind will be able to affect them positively. Additionally, these measurements may identify moderator variables to determine which intervention works best for whom.

## Trial status

Recruitment for this project started in November 2013 and is ongoing until at least the initial minimum sample size with regard to the expected dropout rate is reached.

## Abbreviations

ANOVA: analysis of variance
ASKU: Short Scale for Measuring General Self-efficacy Beliefs
BSI: Brief Symptom Inventory
FMI: Freiburg Mindfulness Inventory
FMPS: Frost Multidimensional Perfectionism Scale
IE-4: Skala internale-externale-kontrollüberzeugung
I-8: Skala Impulsives-Verhalten-8
MANOVA: multivariate analysis of variance
MediMind: Mindfulness-based Stress Prevention Training for Medical Students
RSQ: Response Style Questionnaire
RSS: Rosenberg’s Self-esteem Scale
RSQ: Response Style Questionnaire
SWLS: Satisfaction with Life Scale
TICS: Trier Inventory for the Assessment of Chronic Stress
